## **Executive Summary**

Knee osteoarthritis (KOA) is a prevalent chronic condition globally, contributing to knee pain and disability. Recent studies suggest that high-intensity laser therapy (HILT) holds promise as a treatment for KOA. However, clinical evidence supporting its efficacy, particularly over the long term, remains insufficient. This study aims to (i) assess the short- and long-term effects of HILT as a supplement to rehabilitative activities for individuals with mild to moderate KOA, focusing on joint morphologic changes, and (ii) explore the experiences and perceptions of individuals undergoing this combined intervention. The study will employ both quantitative and qualitative methodologies. The first phase of the study will be a randomized double-blinded controlled trial, which will involve 40 participants with mild-to-moderate KOA based on the Kellgren-Lawrence classification. Participants will be randomly assigned to either the HILT with exercise (HILT+E; n=20) or the placebo laser with exercise group (PL+E; n=20). For eight consecutive weeks, both groups will receive their prescribed laser treatment—HILT (5 W, 1064 nm, 19 to 150 J/cm^2, and 3190 J each session) or a placebo—along with KOA rehabilitation exercises once a week. Examples of KOA rehabilitation exercises are range of motion, stretching, strengthening, and functional training exercises. The exercise prescription will be modified based on the individual's progression. The outcome measures included are knee X-ray (cartilage thickness and joint space), Knee Injury and Osteoarthritis Outcome Score (KOOS), Timed Up and Go (TUG) test, and Numeric Pain Rating Scale (NPRS), which will be evaluated at three different time points by a blinded assessor: baseline, post-intervention, and follow-up after three months of the last session. Knee X-rays (to evaluate cartilage thickness and joint space) will be taken at baseline and follow-up. Two-way repeated measures ANOVA will be used to assess the effects of time, group, and the interaction between the two groups. In the second phase of the study, structured one-to-one interviews will be carried out with participants to explore patient experiences. Each interview will be audio or video-recorded with participants' consent, and questions will be posed in a conversational manner to capture both verbal responses and non-verbal cues. The qualitative data will undergo thematic analysis using ATLAS.ti software programs. The findings of this study are pivotal for deepening our understanding of the impacts of HILT and establishing an effective treatment regimen for KOA. These insights have the potential to improve the pathological condition, providing optimism for mitigating KOA progression.

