4. Numeric Pain Rating Scale (NPRS): This is a tool commonly used to assess pain intensity, utilizing an 11-point scale ranging from 0-10. In this scale, 0 signifies “no pain” while 10

represent the “worst imaginable pain”. The individual are asked to select a single number from this scale that most accurately reflects their current level of pain. A study reported excellent reliability for NPRS with ICC of 0.95.(Alghadir et al., 2018)

5. Knee radiographic imaging, involving X-ray examinations, will be employed to quantitatively assess changes in knee joint structure damage. The examination will only be conducted during baseline and follow-up interval. A qualified radiologist will conduct the knee X-ray examinations to ensure standardized assessments and minimize assessor bias (Lopes et al., 2023) . The evaluation will focus on key parameters, including joint space width, which measures the distance between the femur and tibia to assess joint space narrowing; joint alignment, involving the assessment of angles like the mechanical axis of the leg to identify varus or valgus deformities; and cartilage thickness, measuring articular cartilage thickness in specific knee joint regions to monitor cartilage loss.

The utilization of X-rays as an outcome measure aims to evaluate the severity and progression of KOA by examining changes in joint space, the presence of osteophytes, and the degree of bone or joint destruction(Yang et al., 2022). X-rays are a widely used diagnostic tool for KOA in clinical practice, offering an objective measure of disease progression over time (El-Ghany et al., 2023). The choice of X-rays is practical due to their relatively low cost and widespread availability in clinical and research settings. Extensive research has demonstrated the reliability and validity of using X-rays to assess KOA, showing high inter-observer reliability and moderate-to-high validity compared to other imaging modalities such as MRI or ultrasound (Paraskevas et al., 2023).

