### **3.1.8 Data Analysis**

The data analysis for this study will be conducted using SPSS version 25.0 (SPSS Inc., Chicago, IL, USA) and will adhere to the intention-to-treat principle. All participants, irrespective of their adherence to the intervention, will be included in the analysis. Sociodemographic characteristics of participants at baseline will be described using descriptive statistics and cross-tabulations. The primary statistical analysis for assessing outcomes will involve repeated measures ANOVA, contingent upon meeting assumptions of normality and sphericity. Normality will be evaluated using the Shapiro-Wilk test, with higher values indicating more normal data, while sphericity will be assessed using Mauchly’s test, where lower values closer to 0 suggest more homogenous variance between levels.

The data will undergo two-way repeated measure ANOVA to scrutinize the effects of time, group, and the interaction between the two investigated groups (HILT+E and PL+E). Cohen's d will be applied to ascertain the effect size of each variable, with values of 0.2, 0.5, and 0.8 representing small, medium, and large effects, respectively (Serdar, Cihan et al. 2021). Moreover, the Minimal Clinically Important Difference (MCID) will be considered for the KOOS, NPRS, active knee flexion range, and TUG test to evaluate the clinical relevance of observed changes (Eckhard et al., 2021; Maldaner et al., 2022; Salaffi et al., 2004). All statistical analyses will maintain an alpha level of 0.05 for significance tests (Serdar et al., 2021).

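### The Mauchly criterion that gates the primary repeated measures ANOVA is stated in reverse for W and for its p-value, the scales most likely meant

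*Protocol*

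**What the plan says.** Section 3.1.8 (Data Analysis) names the primary analysis as "repeated measures ANOVA, contingent upon meeting assumptions of normality and sphericity". It then explains how each check is to be read. For normality: "Normality will be evaluated using the Shapiro-Wilk test, with higher values indicating more normal data". For sphericity it names Mauchly's test, "where lower values closer to 0 suggest more homogenous variance between levels". The section does not say whether the values are W, the p-value or the chi-square statistic. It sets no cut-off and names no action for the case where the check fails.

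The model is given next: "The data will undergo two-way repeated measure ANOVA to scrutinize the effects of time, group, and the interaction" between HILT+E and PL+E. On the significance level: "All statistical analyses will maintain an alpha level of 0.05 for significance tests".

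The Executive Summary says of the outcomes "which will be evaluated at three different time points by a blinded assessor: baseline, post-intervention, and follow-up", which gives three visits for KOOS, TUG and NPRS. Section 3.1.4 names KOOS as the primary outcome. For the X-ray, section 3.1.7 says "The examination will only be conducted during baseline and follow-up interval", which is two visits.

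**The concern.** Mauchly's W equals 1 under exact sphericity and falls towards 0 as sphericity breaks down. Its p-value also falls towards 0 as the evidence of violation grows. An analyst who looks at either number and follows the sentence will call badly non-spherical data acceptable, and will call data for which the plain ANOVA is valid unacceptable.

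The sentence matters because the primary analysis is conditional on this check. The group-by-time interaction, where a treatment effect would show, is one of the tests whose level depends on sphericity. Accepting the plain F test when sphericity fails makes that test too liberal. If a correction or an alternative analysis is specified elsewhere for failed sphericity, the reversed rule would call it up for the wrong data sets.

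The wording is also loose on what is tested: sphericity concerns equal variances of the pairwise differences between visits, not equal variances at the visits.

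**Working it through.** The plan gives no W, epsilon or covariance for any outcome, so there is no figure of its own to reproduce. The check has two parts: the direction of the test, and the size of the consequence.

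**Inputs from the Protocol.** Two groups, 40 randomised 1:1 and a 20% dropout allowance (3.1.4); three visits for KOOS, TUG and NPRS (Executive Summary); alpha 0.05 (3.1.8).

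**Assumed.** The degree of non-sphericity, shown as a range, and the number analysed: 40 × (1 − 0.20) = 32, which gives 32 − 2 = 30 error df per contrast. Because 3.1.8 promises to include all participants, 40 (38 df) is shown as well.

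**Direction.** With three visits there are two orthonormal contrasts. With E their pooled within-group sums-of-squares matrix,

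- W = det(E) / (trace(E)/2)²
- chi-square = −(ν − 1) ln W on 2 df, where ν is the error df.

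At N = 40 (ν = 38, multiplier 37):

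| W | chi-square | p |
|---|---|---|
| 1.00 | 0 | 1 |
| 0.85 | 6.01 | 0.049 |
| 0.50 | 25.6 | 0.000003 |
| 0.10 | 85.2 | 3 × 10⁻¹⁹ |

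The 5% critical W is exp(−5.991/37) = 0.85 at N = 40 and exp(−5.991/29) = 0.81 at N = 32. Anything lower is significant evidence against sphericity. So W and p both go to 0 as violation grows, and only the chi-square goes to 0 as sphericity is approached.

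**Size.** For three visits epsilon = 1/(2 − W) exactly, so epsilon lies between 0.5 (W = 0) and 1 (W = 1). The table gives the simulated null rejection rate of the group-by-time test run uncorrected against the 5% point of F(2, 2ν), with 2,000,000 replicates per cell.

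| epsilon | W | 30 error df | 38 error df |
|---|---|---|---|
| 1.0 | 1.00 | 5.0% | 5.0% |
| 0.8 | 0.75 | 6.0% | 6.0% |
| 0.7 | 0.57 | 6.7% | 6.7% |
| 0.6 | 0.33 | 7.5% | 7.5% |
| 0.55 | 0.18 | 8.0% | 8.0% |
| 0.5 | 0 | 8.6% | 8.5% |

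The last row can be confirmed without simulation. At W = 0 only one contrast varies, so the statistic follows F(1, ν). The 5% point of F(2, 60) is 3.150, and P(F(1, 30) > 3.150) = 0.086. For 38 df the point is 3.117 and the probability is 0.0855.

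A separate simulation of 40,000 null trials per pattern at N = 40, using full covariance matrices, agrees:

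| epsilon | median W | uncorrected | Greenhouse-Geisser |
|---|---|---|---|
| 1.00 | 0.96 | 4.9% | 4.7% |
| 0.875 | 0.83 | 5.4% | 4.7% |
| 0.75 | 0.66 | 6.4% | 5.0% |
| 0.61 | 0.35 | 7.5% | 5.0% |
| 0.52 | 0.07 | 8.3% | 4.9% |

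In the last two patterns Mauchly's test rejected in practically every trial. Those are the data sets that the rule as written would pass.

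**What is not touched.** The group main effect is a between-subject test and does not depend on sphericity. With two X-ray visits there is a single contrast, W is 1 by construction and Mauchly's test has no degrees of freedom.

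**The case against.** Three stronger readings are tempting, and the document supports none of them.

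- A reader might infer that the sentence is wrong on every scale. It is not: the chi-square statistic is near 0 when sphericity holds. That scale is unlikely to be meant, because an end point at 0 suits a quantity bounded by 0 and 1, and the neighbouring Shapiro-Wilk wording reads naturally as W or p. But the text does not exclude it.
- A reader might infer that the primary test will go uncorrected whenever sphericity fails. Section 3.1.8 sets no cut-off and does not commit to the uncorrected row of the output. That outcome needs literal use of the sentence and also no correction. A correction is commonly left to the statistical analysis plan, which is not shown here, so the Protocol's silence on it is no finding. SPSS, the named software, also prints the Greenhouse-Geisser row, so an alert analyst may never be misled.
- A reader might infer damage to the X-ray outcomes, since W = 1 would sit at the unfavourable end of the rule. With two visits there is no sphericity assumption to fail and no inflation.

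It is also fair to say that the inflation is modest and that the 8.5% figure is a mathematical ceiling, not an expected case.

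What stands is that on the two likely scales the stated criterion is reversed, and that it sits on the gate to the primary analysis. A prespecified rule should not rely on the analyst overriding it, and settling its meaning after the data are seen would be a post hoc choice on the primary test.

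**Conclusion.** The point holds in a limited form. Section 3.1.8 states the Mauchly criterion in reverse for W and for its p-value. Literal use would accept the plain ANOVA for the wrong data sets and misdirect any remedy specified elsewhere.

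If the F test is then run uncorrected, the level of the time and group-by-time tests on KOOS, TUG and NPRS exceeds 5% by about 1 percentage point at epsilon 0.8, about 2.5 at 0.6, and about 3.5 at most. These sizes rest on assumed covariance patterns. They hardly change between 32 and 40 analysed.

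The endpoint, allocation, sample size and model are not in question. This is a should-fix correction, to be made before analysis.

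**What to change.** Replace the clause on Mauchly's test with: *W near 1 (Mauchly p ≥ 0.05) is compatible with sphericity; W near 0 (p < 0.05) indicates violation.* Add that Greenhouse-Geisser-corrected tests are reported for within-subject effects with more than two visits, at least when Mauchly's test indicates violation.

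The cost is a sentence or two and no extra data or software. Applying the correction always would remove the dependence on Mauchly's test, at the price of a very small loss of power when sphericity holds (simulated level 4.7% against 4.9% uncorrected at N = 40). A mixed model with unstructured covariance needs no sphericity assumption, but it is an optional alternative and is not needed to repair this error.

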### **1.4 Research Objectives**

#### **1.4.1 Main Objectives**

- 1) To examine the long-term effects of high-intensity laser therapy (HILT) combined with rehabilitation exercise on knee pain, physical function, and disability levels among adults with early knee osteoarthritis (KOA).
- 2) To investigate the lived experiences and perceptions of individuals with early knee osteoarthritis undergoing the combined intervention of HILT and rehabilitation exercise.

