### **1.5 Research Hypothesis**

- 1) Combining high-intensity laser therapy with rehabilitation exercise will significantly reduce knee pain, improve physical function, and reduce knee-related disability levels among adults with early knee osteoarthritis in the long term.
- 2) Combining high-intensity laser therapy with rehabilitation exercise will report positive lived experiences and perceptions. These experiences will significantly contribute to improved daily functioning, enhanced quality of life, and overall patient satisfaction compared to those in the control group.
- 3) Combining HILT with rehabilitation exercise will report positive lived experiences and perceptions. These experiences will significantly contribute to improved daily functioning, enhanced quality of life, and overall patient satisfaction compared to those in the control group.

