#### **3.1.4 Sample Size Calculation**

The determination of the sample size for this study will be conducted using G\*Power software version 3.1.9.7, relying on a minimal clinically important difference (MCID) of 11 points for the primary outcome, Knee Injury and Osteoarthritis Outcome Score (KOOS), as indicated by (Eckhard, Munir et al. 2021). We will consider a pre-specified power of 90%, an effect size of 0.3, an alpha level of 5%, and a potential dropout rate of 20%, following the approach outlined by (Serdar, Cihan et al. 2021). Consequently, the necessary total sample size will be 40, with an allocation of 20 participants to each group.

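### For the three-visit outcomes, none of the three tests in the planned repeated measures ANOVA is the long-term difference between the arms, and the protocol does not say which test is primary

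*Protocol*

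**What the plan says.** Section 3.1.8 of the protocol names repeated measures ANOVA as the primary statistical analysis and describes it as a "two-way repeated measure ANOVA to scrutinize the effects of time, group, and the interaction between the two investigated groups". It designates none of the three effects as primary, and it names neither a contrast at a particular visit nor a baseline covariate. It adds: "All statistical analyses will maintain an alpha level of 0.05 for significance tests".

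Section 3.1.7 has KOOS, knee flexion, TUG and NPRS assessed before treatment, at the end of treatment and at a long-term follow-up. X-ray is taken at baseline and follow-up only.

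Main objective 1 (section 1.4.1) is "To examine the long-term effects of high-intensity laser therapy (HILT) combined with rehabilitation exercise on knee pain, physical function, and disability levels". Hypothesis 1 (section 1.5) begins "Combining high-intensity laser therapy with rehabilitation exercise will significantly reduce knee pain, improve physical function" and places the benefit in the long term, without a comparator. Hypotheses 2 and 3 do name the control group. Section 3.1.4 makes KOOS the primary outcome and cites a "minimal clinically important difference (MCID) of 11 points for the primary outcome".

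**The concern.** The protocol fixes its primary model, and for the three-visit outcomes that model does not deliver the quantity the main objective asks for.

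- **Time.** Both arms exercise, so improvement over time says nothing specific about the laser.
- **Group.** This averages all three visits. At baseline, randomisation makes the expected difference zero, so the effect is diluted.
- **Interaction.** This asks whether the two profiles differ in shape anywhere across three visits. A significant result does not say at which visit.

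Three tests at 0.05 with none designated leave room to report whichever is significant. A week-8 difference that has vanished by follow-up could be presented under a long-term objective. Because Hypothesis 1 has no comparator, even a pure time effect fits its wording.

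**Working it through.** **Inputs from the protocol.** 11 points, alpha 0.05, 40 randomised 1:1, 20% dropout (sections 3.1.4 and 3.1.8). Completers: 40 × 0.8 = 32, so n = 16 per arm.

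**Assumptions, since the protocol gives neither an SD nor a correlation.** KOOS SD 15, correlation r = 0.5 between any two visits, equal variances, two-sided contrast. Then d = 11/15 = 0.733.

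**The plan's own figure.** Take the stated effect size of 0.3 as Cohen's f for a within-between interaction, with two measurements and r = 0.5 (all three assumed). Then λ = f²Nm/(1−r) = 0.09 × 32 × 2/0.5 = 11.52 on (1, 30) df, power 90.7%, and 32/0.8 = 40. So 40 reproduces. With three measurements and the same r, 26 suffice, and 26/0.8 = 32.5, rounded up to 33.

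**Group effect, three visits.** For a sustained effect the averaged difference is (0 + d + d)/3 = 2d/3 = 0.489 SD, or 7.3 of the 11 points. λ = (n/2) × 3 × (2d/3)²/(1+2r) = 8 × 3 × 0.239/2 = 2.87 on (1, 30) df, power 37%.

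**Interaction, effect at week 8 only.** The between-arm differences are (0, d, 0). Their squared deviations from their mean sum to 2d²/3 = 0.3585. λ = (n/2) × 0.3585/(1−r) = 8 × 0.3585/0.5 = 5.74 on (2, 60) df, power 54%. With all 40 analysed, λ = 10 × 0.3585/0.5 = 7.17 on (2, 76) df, power 65%. A contrast at follow-up would be significant 5% of the time. The patterns (0, d, d) and (0, 0, d) give the same sum, 2d²/3, so this test has identical power for a short-term-only, a sustained and a late-only effect and cannot tell them apart.

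**Baseline-adjusted contrast at follow-up.** Noncentrality is d√(n/2)/√(1−r²) = 0.733 × 2.828/0.866 = 2.395. Multiplying by √(28/29) for the estimated covariate gives 2.353 on 29 df, power 62%.

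**Comparison, 32 completers, SD 15, r = 0.5:**

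| Difference at week 8, follow-up (points) | Interaction | Adjusted follow-up contrast | Gain |
|---|---|---|---|
| 11, 11 (sustained) | 54% | 62% | +8 |
| 5.5, 11 (half-grown at week 8) | 42% | 62% | +20 |
| 16.5, 11 (fading) | 80% | 62% | -17 |

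Gains are taken before rounding. For a sustained effect, r = 0.7 gives 79% against 78%, and r = 0.8 gives 91% against 92%. With 20 per arm, SD from 12 to 20, r from 0.3 to 0.7 and these three patterns, the gain runs from about -22 to +27 points. A simulation of 20,000 trials at 20 per arm (sustained, SD 15, r = 0.5) gave 64.9% for the interaction and 73.4% for the adjusted contrast, against 64.8% and 73.0% by formula.

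**X-ray, two visits.** The 1-df interaction is the difference between arms in change from baseline to follow-up. Adjusting for baseline instead of taking the change multiplies the variance by (1−r²)/[2(1−r)] = (1+r)/2, which is 0.75 at r = 0.5, a 25% reduction.

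**The case against.** The strongest reply is that the interaction is a legitimate test and fits part of the plan. Research question 1 and specific objective 1 ask about short- and long-term effects together, and a joint test over both post-baseline visits addresses that. Baseline is used as the reference for differential change, and the choice between ANCOVA and repeated measures ANOVA in a randomised trial is largely one of efficiency. Contrasts and covariates are often left to a statistical analysis plan, which may exist but is not shown. The comparator is clear elsewhere: the introduction and section 3.1.1 set out a placebo-laser comparison.

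Much of this stands. A reader might infer that the ANOVA is invalid, but it is not. A reader might infer a fixed power gain from adjustment, but the protocol gives no SD, correlation or time course to support one, and if the effect fades the proposed contrast has less power. A reader might extend the point to X-ray, where the interaction already matches the long-term question apart from precision. A reader might infer that the investigators mean to treat a time effect as proof; nothing in the protocol says so.

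What does not stand is that the joint test answers main objective 1. The point is not that detail is absent: section 3.1.8 itself fixes the primary model, and a contrast set elsewhere would have to supplement or replace it.

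**Conclusion.** The point holds for KOOS, knee flexion, TUG and NPRS. The primary analysis leaves three candidate tests open, and none is the difference between arms at the long-term visit. The dilution of the group effect to 2d/3 and the inability of the 2-df test to locate a difference are structural and need no assumed SD or correlation. The 54% chance of a significant interaction without any long-term effect rests on 11 points at week 8, SD 15, r = 0.5 and 32 completers.

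The case for change is that the test should match the objective; power is secondary and can only be given as a range. The omnibus test's advantage under a fading effect comes from the week-8 difference, which is not the long-term question. This should be corrected, but it does not invalidate the trial.

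**What to change.** In section 3.1.8, make the primary result the baseline-adjusted difference in KOOS between arms at the long-term visit with a 95% confidence interval, from a model with the baseline value as covariate and group, visit and group-by-visit as terms. Report the week-8 contrast from the same model as secondary, use the same model for the other three-visit outcomes, and present time and within-group changes descriptively. For X-ray, use ANCOVA on baseline for precision. In Hypothesis 1, add *compared with placebo laser plus exercise*. Section 3.1.7 labels the long-term visit both week 12 and week 24; this must be reconciled before the contrast can name a week.

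The cost is wording only, since the baseline values are already collected. The one downside is lower power than the omnibus test if the effect fades after week 8.
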